### General therapy for AECOPD

All participating patients, regardless of the study arm into which they are randomized, will be monitored and managed following the recommendations of the 2017 GOLD guidelines [1] and according to each center’s specific expertise and clinical routine.

The following approaches should be considered (but are not mandatory) for the use of bronchodilators: increasing doses and/or frequencies of short-acting bronchodilators, if required; the combination of short-acting beta2-agonists and anticholinergics, if required; the use of long-acting bronchodilators, if the patient becomes stable; and the use of spacers or air-driven nebulizers, when appropriate. Corticosteroids (oral/intravenous) should be considered if needed. Antibiotics (oral/intravenous) are considered when signs of bacterial infection are present. The specific drugs used and the dosing regimens will be left up to the attending physician.

At all times, the following procedures should be followed: monitoring fluid balance, considering subcutaneous heparin or low molecular weight heparin for thromboembolism prophylaxis, and identifying and treating associated conditions (e.g., heart failure, arrhythmias, and pulmonary embolism).

The study protocol requires that routine monitoring include measurements of noninvasive blood pressure, pulse oximetry, and electrocardiography. Every patient should receive at least one peripheral venous line to receive intravenous treatments during the study period. Nasogastric tubes, urinary bladder catheters, and/or other intravenous catheters may be used at the discretion of the attending physician, following established protocols at each center. Any decision affecting the protocol will be recorded in the case report form (CRF).

### Data collection and definitions

At each study center, patient data will be collected using that center’s dedicated pseudonymous CRF, and the CRFs will be stored in locked file cabinets in areas with limited access. Data will be transmitted to the coordinating center whenever a patient dies or is discharged from the hospital, and follow-up data will be transmitted to the coordinating center when follow-up is complete. In addition, the coordinating center will have direct access to the cloud platform to extract the data related to the NPPV parameters. Before the data are exported into a computerized database at the coordinating center, two trained data collectors from the coordinating center will check the completeness and quality of information. Logical checks will be performed for missing data and to determine inconsistencies. If required, the data collector will contact the investigator by phone to validate or reformat the data for entry into the database. Then all data entry will be performed separately by two trained data collectors, and their work will be checked by another two collectors. Only the principal investigator and the data managers at the coordinating center will have access to the final database.

At enrollment, patients’ baseline characteristics will be recorded: demographics, medical history, history of NPPV use, history of steroids and/or inhalation therapy use, smoking status, spirometry (forced ventilatory capacity and forced expiratory volume in 1 s), Acute Physiology And Chronic Health Evaluation (APACHE) II score, vital signs (including heart rate, RR, arterial blood pressure, SpO_2_), dyspnea score, scale for the use of accessory muscles, Glasgow coma scale (GCS) score, arterial blood gases (including pH, PaO_2_, PaCO_2_, bicarbonates, and lactates), and routine laboratory tests (including hemoglobin, white blood cell count, platelet count, prothrombin time, partial thromboplastin time, creatinine, blood urea nitrogen, alanine aminotransferase, aspartate aminotransferase, and bilirubin).

At 2, 6, 24, and 48 h after randomization, vital signs, dyspnea score, scale for the use of accessory muscles, GCS score, supplemental oxygen flow, and arterial blood gases will be recorded.

All NPPV parameters will be continuously monitored by the built-in pneumotachograph and uploaded to the cloud platform, which will provide data continuously over a wireless network. Peak inspiratory pressure (PIP), EPAP, exhaled *V*_T_, frequency, exhaled minute volume (*V*_m_), and leak at 2, 6, 24, and 48 h after randomization will be extracted from the cloud platform and recorded with those averaged values over 5 min at the indicated time points. In addition, maximal PIP, maximal EPAP, daily time of NPPV use (hours) over the first 5 days, and total time of NPPV use (days and hours) will be recorded by the cloud platform. Complications related to NPPV will be monitored and recorded.

NPPV tolerance will be recorded on a 4-point scale and then dichotomized into acceptable (score of 2 or 3) or poor (score of 0 or 1) tolerance [31]. The dyspnea score will be assessed using a verbal analog scale with scores from 0 (no dyspnea) to 10 (maximum dyspnea). The use of accessory muscles will be assessed according to the following scale: 0, no visible tonic or phasic use of neck muscles; 1, neck muscles taut but with no respiratory modulation (i.e., tonic activity); 2, mild respiratory modulation in neck muscle contraction; 3, moderate phasic activity (no supraclavicular or intercostal indrawing); 4, vigorous phasic activity with indrawing; and 5, vigorous phasic activity with abdominal paradox [32]. To determine PaO_2_/FiO_2_ ratios while patients are receiving NPPV, FiO_2_ will be calculated using the following conversion factor: (21% + [3% × oxygen flow in L/min of supplemental oxygen]). This provides an approximation of percent oxygen delivered, is influenced by minute ventilation and breathing patterns, and may be inaccurate if air leakage occurs around the mask or through the mouth [33].

### Endpoints and follow-up

The primary endpoint is the NPPV failure rate, defined as the need for endotracheal intubation and invasive ventilation at any point during the study. Secondary endpoints include decrement of PaCO_2_ from baseline to 2 h after randomization, hospital mortality, 28-day mortality, and 90-day survival, as well as actual intubation rate, intensive care unit (ICU) admission, hospital stay, hospital costs, ventilator-free days within 28 days, hospital-free days within 90 days, and 90-day hospital readmission.

All patients will be monitored until hospital discharge or until day 90 in cases where the patients remain at the hospital. After discharge, follow-up will be performed by phone on days 28 and 90 after randomization, and the following will be recorded: 28-day mortality, ventilator-free days within 28 days, hospital-free days within 90 days, 90-day survival, and 90-day hospital readmission.

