**Methods/design:**

The HAPPEN study is a multicenter, two-arm, single-blind, prospective, randomized controlled trial. In total, 600 AECOPD patients with low to moderate hypercapnic respiratory failure will be included and randomized to receive high-intensity or low-intensity NPPV, with randomization stratified by study center. The primary endpoint is NPPV failure rate, defined as the need for endotracheal intubation and invasive ventilation. Secondary endpoints include the decrement of arterial carbon dioxide tension from baseline to 2 h after randomization, in-hospital and 28-day mortality, and 90-day survival. Patients will be followed up for 90 days after randomization.

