### Study population

During screening and prior to enrollment in the study, patients will be considered eligible for the study if they are diagnosed with AECOPD as defined by the criteria of the Global Initiative for Chronic Obstructive Lung Disease (GOLD) in 2017, with arterial pH < 7.35 and ≥ 7.25, and PaCO_2_ > 45 mmHg [1].

Patients will be excluded from study participation if any of the following criteria are present: age < 18 years; excessive amount of respiratory secretions or weak cough; upper airway obstruction; recent oral, facial, or cranial trauma or surgery; recent gastric or esophageal surgery; severe abdominal distension; active upper gastrointestinal bleeding; cardiac or respiratory arrest; pH < 7.25; arterial oxygen tension/fraction of inspired oxygen (PaO_2_/FiO_2_) < 150 mmHg; pneumothorax; severe ventricular arrhythmia or myocardial ischemia; severe hemodynamic instability despite fluid repletion and use of vasoactive agents; severe metabolic acidosis; lack of cooperation; and refusal to receive NPPV [29]. Patients will also be excluded if they have a do-not-intubate order or refuse research authorization.

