### NPPV weaning and failure

For all patients, the levels of IPAP and EPAP and the daily use of NPPV can be gradually decreased under conditions of clinical stability, defined as the presence of the following: the improvement or resolution of the underlying cause of AECOPD, RR < 25 breaths/min, heart rate < 110 beats/min, arterial pH < 7.35, and PaO_2_ > 60 mmHg at FiO_2_ ≤ 0.4. Attempts to withdraw NPPV are made if IPAP is decreased to 10–12 cmH_2_O, EPAP is 5 cmH_2_O, or daily use is less than 5 h. Weaning is considered successful if, for 72 h after withdrawal, patients are able to sustain spontaneous breathing without signs of respiratory distress, defined as the presence of at least two of the following: arterial pH < 7.35; RR > 30 breaths/min; PaO_2_ < 60 mmHg or arterial oxygen saturation measured by pulse oximetry (SpO_2_) < 90% at FiO_2_ ≥ 0.4; retraction of the intercostal spaces, use of accessory respiratory muscles, or thoracic–abdominal paradoxical movement; or decreased consciousness, agitation, or diaphoresis [30]. By contrast, when patients present with the aforementioned signs of respiratory distress after withdrawal, weaning is considered to have failed and NPPV is resumed.

Endotracheal intubation is considered if a patient has either arterial pH < 7.25 with PaCO_2_ > 20% greater than the baseline or PaO_2_ < 60 mmHg despite maximum tolerated supplemental oxygen, and if at least one of the following criteria is met: clinical signs suggestive of severely decreased consciousness (e.g., coma, delirium); excessive amount of respiratory secretions with weak cough; use of accessory respiratory muscles or thoracic–abdominal paradoxical movement; severe upper gastrointestinal bleeding with aspiration or vomiting; or severe hemodynamic instability, despite fluid repletion and use of vasoactive agents [29]. If a patient fulfills one of these criteria, the final decision for intubation is made by the attending physician, with the consent of the patient’s next of kin or other surrogate decision makers, as appropriate.

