### Statistical analysis

We will report continuous variables as means ± standard deviations or medians and interquartile ranges, when appropriate, and categorical variables as proportions.

Continuous variables will be compared using an appropriate parametric (Student’s *t* test) or nonparametric (Mann–Whitney *U* test) method. Categorical variables will be compared using a chi-square test or Fisher’s exact test, if appropriate. A linear mixed model with two factors (study group and time) will be used to analyze variables repetitively measured over time; Bonferroni’s adjustment for multiplicity of tests will be used in post hoc comparisons to ensure that the total error rate will not exceed 0.05.

We will use a chi-square test or Fisher’s exact test to compare the primary outcome and secondary dichotomous outcomes, and a parametric (Student’s *t* test) or nonparametric (Mann–Whitney *U* test) method to compare secondary continuous outcomes, as appropriate. For the primary and secondary outcomes, we will calculate between-group differences in risk for dichotomous outcomes, between-group median differences (using Hodges–Lehmann estimates) for continuous outcomes with non-normal distributions, and between-group mean differences for continuous outcomes with normal distributions, all with 95% confidence intervals. The baseline characteristics will be tested for imbalance. If imbalances are found (despite the 1:1 randomization of a relatively large cohort), the primary and secondary outcome variables will be analyzed using a multiple logistic regression model, adjusted for possible baseline imbalances.

Cumulative event rates for the primary and secondary endpoints involving time-to-event data will be estimated for the two groups using the Kaplan–Meier method and compared using a log-rank test. Hazard ratios, their 95% confidence intervals, and *P* values for the comparison of the two treatment groups will be determined using the Cox regression model.

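### Deaths in hospital without a need for intubation count as non-failures in the primary NPPV failure rate; an intubation-or-death sensitivity analysis should be prespecified beside it

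*Protocol article*

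**What the plan says.** Under Endpoints and follow-up the protocol article gives the primary endpoint as the NPPV failure rate, "defined as the need for endotracheal intubation and invasive ventilation at any point during the study". The abstract (Methods/design) has the same content: "The primary endpoint is NPPV failure rate, defined as the need for endotracheal intubation and invasive ventilation". Neither includes death. Death enters only among the secondary endpoints, listed as "hospital mortality, 28-day mortality, and 90-day survival, as well as actual intubation rate". That list also shows that actual intubation is a different endpoint from the primary one.

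The criteria on which need rests are under NPPV weaning and failure. A blood-gas condition is required (pH below 7.25 with PaCO2 more than 20% above baseline, or PaO2 below 60 mmHg despite maximum tolerated oxygen), "and if at least one of the following criteria is met: clinical signs suggestive of severely decreased consciousness" or one of four other listed clinical conditions. Neither death nor cardiac or respiratory arrest is listed. Once criteria are fulfilled, "the final decision for intubation is made by the attending physician", with consent from next of kin or a surrogate.

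Under Statistical analysis: "We will use a chi-square test or Fisher’s exact test to compare the primary outcome and secondary dichotomous outcomes". The intention-to-treat analysis keeps all patients in their randomized groups. Missing data are handled by last observation carried forward. No sentence says how a death without need for intubation is classified.

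**The concern.** An endpoint named NPPV failure should separate patients whom NPPV carried through from those whom it did not. As defined, it puts two opposite outcomes in the same cell: weaned alive, and died in hospital without meeting the criteria. Death also ends the patient's chance of meeting the criteria later. If one arm has more such deaths, and some of those patients would otherwise have gone on to need intubation, that arm's failure rate falls for a reason that is not a benefit.

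The trial's hypothesis is that higher pressure reduces intubation and improves survival. A lower failure rate would be read as better ventilatory support, and superiority is also the question at the interim analysis. The reader of the primary result needs to know whether it holds when these deaths are counted.

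**Working it through.** **1. How each outcome is scored.** From the definition, the criteria and the binary test:

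| In-hospital course | Primary score |
|---|---|
| Weaned alive | non-failure |
| Criteria met, intubated | failure |
| Criteria met, not intubated | failure on the natural reading of need, but not stated |
| Died, criteria never met | non-failure, by implication |

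The last row is the point at issue. The third row needs one clarifying sentence.

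**2. Inputs.** From Sample-size calculations and interim analyses: 15% (low intensity) vs 6% (high intensity), two-sided alpha 0.05, 480 evaluable, 20% dropout, 600 enrolled. Allocation is 1:1, so 240 or 300 per arm. The rate of deaths without criteria is not given, so every death rate below is an assumption.

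**3. The plan's own figures.** 480/(1 − 0.20) = 600 reproduces. Power uses the normal approximation Φ{[|p1 − p2| − 1.96·√(2p̄(1 − p̄)/n)] / √[(p1(1 − p1) + p2(1 − p2))/n]}. At n = 240, p̄ = 0.105, this is Φ[(0.09 − 1.96 × 0.02798)/0.02768] = 0.898, not the stated 81%. At n = 300 it is 0.951. That mismatch is a separate matter; 0.898 and 0.951 are the baselines for step 6.

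**4. How many uncounted deaths would matter.** Uncorrected chi-square, 300 per arm, with extra deaths in the high-intensity arm counted as failures:

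| Low vs high | P |
|---|---|
| 45 vs 18 (planned 15% vs 6%) | 0.0003 |
| 45 vs 22 (4 deaths added to 18) | 0.003 |
| 45 vs 29 (11 added) | 0.047 |
| 45 vs 30 (12 added) | 0.064 |

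At the planned effect it takes 12 extra deaths, 12/300 = 4% of that arm, to cross 0.05. With a smaller observed effect, 45 vs 28 (28/300 = 9.3%), P = 0.034, and two added deaths give 45 vs 30, P = 0.064. The standard error of the risk difference at the planned rates is √(0.15·0.85/300 + 0.06·0.94/300) = 0.0248, so four deaths (1.3 points) are about half a standard error.

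**5. Chance of a spurious win.** Suppose intubation-or-death is truly 15% in both arms, but in the high-intensity arm x points of it are deaths without criteria that replace intubations, with none in the other arm. The endpoint as written then compares 15% with 15% − x. The probability of a significant result favouring high intensity, against a nominal 2.5%, is:

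| x | 240 per arm | 300 per arm |
|---|---|---|
| 1 point | 5% | 5% |
| 2 points | 9% | 10% |
| 3 points | 16% | 19% |
| 5 points | 38% | 46% |

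**6. Power of the composite.** Add the same rate of such deaths to both arms, so the 9-point difference is unchanged:

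| Deaths in each arm | Composite rates | 240 per arm | 300 per arm |
|---|---|---|---|
| 0% | 15% vs 6% | 0.90 | 0.95 |
| 2% | 17% vs 8% | 0.85 | 0.92 |
| 3% | 18% vs 9% | 0.82 | 0.90 |
| 5% | 20% vs 11% | 0.78 | 0.86 |

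**The case against.** The strongest reply is that the endpoint is need for intubation and that actual intubation is listed separately. A reader might infer that do-not-intubate orders written after entry (the protocol says only "Patients will also be excluded if they have a do-not-intubate order"), physician discretion or a surrogate's refusal turn failures into successes. The documents do not support that: a patient who meets the criteria and is not intubated can still count under need. This stands, and it narrows the gap to deaths in which the criteria were never met.

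That group may be small. Entry excludes arrest, severe haemodynamic instability, pneumothorax and severe hypoxaemia. Patients are watched at the bedside, with blood gases at 2, 6, 24 and 48 h, and many patients dying of ventilatory failure would meet the criteria first. This also stands, but it limits the size without settling it.

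A reader might further infer that the scoring hides harm, or that it favours high intensity. Neither follows. Hospital mortality, 28-day mortality and 90-day survival are compared by arm, and the data and safety monitoring board reviews safety. Pneumothorax and hypotension are listed as possible complications of NPPV in general, not of the high-pressure arm. Nor does every excess death lower a failure rate: a death in a patient who would never have needed intubation leaves it unchanged.

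Finally, need for intubation matches the primary hypothesis and the sample-size basis, whereas a composite has no planning rate in the protocol. That is a fair reason not to replace the primary endpoint. What remains is that separate mortality comparisons do not show whether the primary contrast survives once these deaths are counted.

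**Conclusion.** The concern holds in a limited form. By its definition, stated in two places, the primary endpoint scores a hospital death without need for intubation as a non-failure, and nothing in the article corrects this. Bias in the comparison requires that such deaths differ by arm and stand in for intubations that would otherwise have happened.

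The size cannot be established from the documents. It is minor at the planned effect, where 12 extra deaths in one arm are needed to lose nominal significance, and material for a borderline result, where two can suffice. The direction is unknown. The death rates behind the spurious-win and power figures are illustrative, and all P values use the nominal 0.05 without adjustment for the single interim look.

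This is an inexpensive improvement that limits what may be concluded from the primary result. It is not a ground for changing the primary endpoint or for making the superiority claim conditional on two analyses.

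**What to change.** Keep need for intubation as the primary endpoint. In Endpoints and follow-up:

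- State that a patient who meets the intubation criteria but is not intubated, for whatever reason, counts as an NPPV failure.
- Prespecify a sensitivity analysis of need for intubation or death before hospital discharge, tested and estimated in the same way as the primary outcome.
- Tabulate deaths without need for intubation by arm beside the primary result.
- State that, if the two analyses disagree, the report will not describe the primary result as fewer NPPV failures without that qualification.

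The cost is one analysis and one table. No new data are needed, since hospital mortality is already a secondary endpoint. The drawback is that deaths unrelated to ventilation dilute the composite. With 5% such deaths in both arms its power at 240 per arm is 0.78, below the stated 81%, which is a further reason to use it as a sensitivity analysis and not as the primary test.

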### Study dropouts

Because participation is voluntary, patients have the right to withdraw consent to participate at any time for any reason, without any unfavorable consequences for further medical treatment. Furthermore, investigators have the right to terminate the participation of any patient at any time if the investigator deems it to be in the participant’s best interest. The reasons and circumstances for study discontinuation will be documented in the CRF.

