### Randomization and blinding

Randomization will be accomplished by a computer-generated random number sequence, stratified by study center, with an allocation ratio of 1:1 for each group. The generation of sequences and their storage will be managed by an independent information technology expert who is not involved in this study. Each allocation sequence will be concealed from the coordinating center through the use of numbered, opaque, and sealed envelopes, and will be managed by an independent employee at the coordinating center who is not involved in this study. The randomization number will consist of a patient identification number of nine digits, in which the first four digits correspond to the identifier of the study center, the middle three correspond to the patient inclusion number at the respective center, and the remaining two correspond to the NPPV-strategy identifier. An independent telephone-contact system will be used for randomization. All investigators at each of the participating centers will immediately contact an independent employee of the coordinating center to obtain a randomization number if a patient fulfills the inclusion criteria. Within 1 h of the validation of the inclusion criteria, patients will be randomly assigned to undergo either high-intensity or low-intensity NPPV. Patients will continue to receive their current therapy prior to randomization assignment.

At each study center, at least two investigators will be conducting the study: one to perform the interventions defined in the protocol, and the other, who will be blinded to the intervention, to perform the data collection. All data related to the NPPV parameters will be extracted from a cloud platform by an independent information technology expert not involved in this study; all data analyses will be performed in a blinded fashion.

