### Sample-size calculations and interim analyses

The calculation of the sample size was based on our primary hypothesis that in AECOPD patients high-intensity NPPV leads to a reduced need for endotracheal intubation compared to low-intensity NPPV. Our previous clinical experience and previous studies [18–20] led us to anticipate that the need for endotracheal intubation would be 15% for the low-intensity NPPV group. Based on the assumption that the need for intubation could be reduced to 6% in the high-intensity NPPV group, we estimated that a minimum sample size of 480 patients would be required to detect a between-group difference of 9% for the need for intubation, with an 81% power and a two-tailed alpha level of 0.05, using superiority tests for two proportions. Assuming a dropout rate of 20%, we calculated that 600 patients should be enrolled.

Interim analysis to assess superiority is scheduled, and it will take place at hospital discharge of the first 300 randomized patients. The criteria for premature discontinuation of the study, based on the results of this single interim analysis, will be those defined by O’Brien and Fleming [34]. It will be performed at the coordinating center by an independent data and safety monitoring board (DSMB). The DSMB will meet by conference call, and DSMB discussions will take place by email or conference call.

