In case of loss to follow-up or consent withdrawal, the causes will be reported. Intention-to-treat (ITT) and per protocol (PP) analyses will be conducted. For the ITT analysis, data will be processed for all trial patients in the groups in which they were randomized. A PP analysis will be performed as a sensitivity analysis in the case of any loss to follow-up, a missing primary endpoint, or any protocol deviation that might lead to a biased conclusion. Missing data will be handled using the “last observation carried forward” method.

All tests will be two-sided. Differences with *P* values of less than 0.05 will be considered statistically significant, except for those incorporating multiple comparisons. Statistical analyses will be performed using SPSS software (version 19.0, SPSS Inc., Chicago, IL, USA).

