The HAPPEN study protocol has limitations which must be addressed. First, the study is being performed in patients with mild to moderate respiratory acidosis, which suggests that the results may not be generalizable to the whole population. Further study will be required to assess whether our findings can be extended to other subgroups and the whole population. Second, despite the blinding of patients to the intervention, blinding of investigators is not possible due to the nature of the intervention, and this could induce bias. However, at each study center, at least two investigators will be working. One investigator will perform the interventions, as defined in the protocol. The second investigator, who will be blinded to the intervention, will collect data. Moreover, all data related with the parameters of NPPV will be extracted, and all data analyses will be performed in a blinded fashion. Third, even if protocol interventions represent a consensus among centers, between-center differences in the experience of NPPV use may still affect the results of this study. Fourth, several confounding factors associated with general therapy for AECOPD (e.g., the use of bronchodilators, corticosteroids, and antibiotics; fluid administration; thromboembolism prophylaxis; treatment of associated conditions) are only suggested and are not protocolized. Nevertheless, the study protocol stresses that general therapy is to be performed in accordance with each center’s specific expertise to ensure that the trial is as close as possible to routine clinical care.

In summary, the HAPPEN study will be the first randomized controlled study to investigate whether high-intensity NPPV better corrects hypercapnia and reduces the need for intubation and mortality in AECOPD patients than low-intensity NPPV. The results of the HAPPEN study will help critical care physicians choose the intensity at which to deliver NPPV to AECOPD patients.

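### The dropout rule lets investigators, including the one who knows the arm, end a patient's trial participation without separating this from stopping the assigned NPPV, so informative primary outcomes can go unobserved

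*Protocol article*

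**What the plan says.** The Study dropouts section of the protocol article covers two routes out of the trial. The patient may withdraw consent, and "investigators have the right to terminate the participation of any patient at any time", on the condition that the investigator judges this to be best for the participant. The record then required is limited: "The reasons and circumstances for study discontinuation will be documented in the CRF".

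On who knows the arm, the Discussion concedes that "blinding of investigators is not possible due to the nature of the intervention, and this could induce bias". Randomization and blinding provides for at least two investigators per center, "one to perform the interventions defined in the protocol, and the other, who will be blinded to the intervention, to perform the data collection".

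Endpoints and follow-up counts the primary endpoint, need for intubation and invasive ventilation, whenever it occurs during the study. It has all patients monitored to discharge, or to day 90 if still in hospital, with calls on days 28 and 90. Under Statistical analysis, the ITT rule is that "data will be processed for all trial patients in the groups in which they were randomized". The same section foresees a missing primary endpoint, for which it adds a per-protocol sensitivity analysis, and handles missing data by last observation carried forward. The sample-size section reads: "Assuming a dropout rate of 20%, we calculated that 600 patients should be enrolled".

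**The concern.** The right is to end participation, not merely to stop the assigned ventilation strategy. It stands beside consent withdrawal under a heading about dropouts, and its result is called study discontinuation. A treatment decision is thus written as a study exit.

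Three features make this more than routine wording here. First, the investigator delivering NPPV knows the arm and is a natural person to make a best-interest judgement. Second, that judgement is likeliest when a patient worsens or tolerates NPPV badly, and the Background itself links poor tolerance and discontinuation to intubation. The patients who might leave are therefore at raised risk of the primary event. Third, the endpoint is counted during the study, so ending participation can close the window in which it is observed, although the patient may still be on the ward where intubation and death can be seen.

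At stake is the primary comparison and, by the same route, 28-day mortality and 90-day survival. ITT fixes who is analysed and in which arm, but does not supply an outcome that was not observed.

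**Working it through.** **The plan's own figures.** The dropout step reproduces: 480 / (1 − 0.20) = 600. The step before it does not: 15% vs 6% at two-sided 0.05 and 81% power needs 186 per arm (372 in total) by the pooled normal formula, and 480 patients give 89.8% power. That discrepancy is conservative and separate from this point.

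**Inputs.** Failure rates of 15% (low intensity) and 6% (high intensity), two-sided alpha 0.05 and 600 patients come from the sample-size section; the 1:1 ratio comes from Randomization and blinding. Hence n = 300 per arm. Expected failures are 0.15 × 300 = 45 and 0.06 × 300 = 18, or 63 in all. The dropout allowance is 0.20 × 600 = 120.

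**Assumptions, not in the documents.** A fraction f of would-be failures leaves before the event and is scored as no event. There is one final pooled two-proportion test, ignoring the interim look.

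**Formula.** Observed rates are L = true low rate × (1 − f_low) and H = true high rate × (1 − f_high). With D = L − H and m = (L + H)/2:

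- SE0 = √[2m(1 − m)/n]
- SE1 = √{[L(1 − L) + H(1 − H)]/n}
- P(significant result for high intensity) = 1 − Φ[(1.96·SE0 − D)/SE1]

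**No true effect (15% in both arms), 20% lost in high intensity only.** That is 0.20 × 45 = 9 patients, 3% of the arm. L = 0.150, H = 0.120, D = 0.030, m = 0.135, SE0 = 0.02790, SE1 = 0.02788. (0.05469 − 0.030)/0.02788 = 0.886, so P = 0.188.

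**True 15% vs 6%, 20% lost in low intensity only.** L = 0.120, H = 0.060, D = 0.060, m = 0.090, SE0 = 0.02337, SE1 = 0.02324. (0.04580 − 0.060)/0.02324 = −0.611, so P = 0.729. With no loss, P = 0.951.

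| True low / high | f high | f low | Observed low / high | P(significant for high intensity) |
|---|---|---|---|---|
| 15 / 15 | 0 | 0 | 15.0 / 15.0 | 2.5% |
| 15 / 15 | 0.1 | 0 | 15.0 / 13.5 | 7.6% |
| 15 / 15 | 0.2 | 0 | 15.0 / 12.0 | 18.8% |
| 15 / 15 | 0.4 | 0 | 15.0 / 9.0 | 61.9% |
| 15 / 15 | 0.2 | 0.2 | 12.0 / 12.0 | 2.5% |
| 15 / 6 | 0 | 0 | 15.0 / 6.0 | 95.1% |
| 15 / 6 | 0 | 0.2 | 12.0 / 6.0 | 72.9% |
| 15 / 6 | 0 | 0.4 | 9.0 / 6.0 | 28.6% |
| 15 / 6 | 0.2 | 0.2 | 12.0 / 4.8 | 89.1% |

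Excluding the lost patients instead of scoring them as no event changes little: with f = 0.2 in high intensity only, the observed rate is 0.120/0.97 = 12.4%, still below 15%.

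**The case against.** The best case for the plan is that the article never says outcome collection stops at termination. It says all patients are monitored to discharge or day 90, promises ITT, and condenses a full protocol (version 6) that may settle the matter. Best-interest withdrawal is ordinary participant protection, reasons are documented, and the data and safety monitoring board reviews adherence and completeness. The protocol also gives other routes for the patients in question: IPAP may be lowered for tolerance, a nasal mask may be substituted, and a deteriorating patient meets intubation criteria that lead toward the endpoint rather than out of the trial.

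Much of this stands as a limit on the claim. A reader might infer that data collection certainly ends at termination; the article does not say so. A reader might also infer that only the unblinded investigator holds the right; the text says investigators in general, and each center has a blinded one too.

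Nor does the article support a bias in favour of high intensity. Both arms are titrated to tolerance. High intensity is pushed further (up to 30 against 20 cmH2O), but the Background and Discussion expect poor tolerance under low intensity and more comfort under high intensity.

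The objection does not remove the point. The rule as written concerns participation, and it requires nothing after exit beyond reasons and circumstances. The general monitoring sentence does not address terminated patients, and the analysis section itself expects some missing primary endpoints. Blinded data collection and analysis do not constrain who is removed.

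**Conclusion.** The concern holds as a defect in how the rule is fixed: stopping the assigned strategy and leaving follow-up are merged, in the hands of investigators who include one aware of the arm. The passages on dropouts, follow-up and ITT need to be reconciled.

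Modest unequal loss would matter. About 9 would-be failures lost from the high-intensity arm alone would raise the chance of a false benefit from 2.5% to about 19% if there is no true effect. The same 20% lost from the low-intensity arm alone would cut power from about 95% to 73% at 15% vs 6%. Equal fractions lost leave the false-positive rate at 2.5% and power at about 89%. These sizes rest on assumed loss fractions and on scoring the lost patients as not intubated; the documents give no termination rate, and the direction is undetermined.

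Larger figures are tempting but unsupported. If 10% of the high-intensity arm alone (30 patients) were removed and half would have been intubated, the chance of a false benefit would be about 46%. The arithmetic is right, but it needs 15 of 45 would-be failures to vanish from one arm and none from the other. Likewise, the 120-patient dropout allowance covers loss of every kind, including consent withdrawal, and is not a forecast of investigator removals.

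**What to change.** Reword the Study dropouts section so that an investigator's decision to stop the assigned strategy does not end outcome collection. Need for intubation, actual intubation, hospital outcome and the day-28 and day-90 calls then continue for every randomized patient, analysed in the randomized arm, unless the patient or surrogate withdraws consent to data collection. Record strategy stopped and follow-up consent withdrawn as separate CRF items, and report both by arm. If the full protocol already says this, the published text needs only a sentence to match. Clinical discretion to stop NPPV is unchanged.

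The cost is a wording amendment and one CRF line. No visits are added, because the inpatient data and both calls are already planned. The downside is slight dilution of the effect from patients who are off their assigned strategy but stay in the ITT set.
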